### Handling and storage of data

The study will be conducted according to good clinical practice standards. The handling of personal data will comply with the Personal Data Protection Act 2012 and local data protection regulations. Data collected from EHR systems and mobile/web applications using the TRANSFoRm system will be stored in a secure site hosted by Custodix (a private company specialising in data protection solutions in eHealth). TRANSFoRm has implemented technical measures to ensure that identifiable personal data is protected and that study data in the TRANSFoRm study system is protected by access authorisation and pseudonyms. Data for the control group will be transcribed from the paper-based forms via a web-based clinical data capture system hosted on a secure data repository at King’s College London. At the end of the study, all data will be securely transferred to Custodix to create the analysis dataset. This will only contain pseudonymised data. After analysis and reporting, data will be archived at the Karolinska Institutet in Stockholm for 15 years.

## Discussion

Recruitment failures in primary care are common due to the complexity of recruiting patients in this setting. To date, the most effective method for recruiting patients to primary care trials is opportunistic recruitment. This is performed manually using paper- or web-based case report forms and relies on busy GPs actively approaching potentially eligible patients in the consultation room and inviting them to take part. In an increasingly demanding healthcare system, such methods are highly time-consuming, and as a result, many studies fail to achieve their recruitment targets or to even recruit a single patient [1,19,20]. Recent advancements in information technology have enabled researchers, technologists and clinicians to collaborate with the aim to develop systems that can overcome these challenges and support effective recruitment. The TRANSFoRm system aims to transform patient recruitment and follow-up in primary care by automating the processes for identifying, recruiting and following up patients, potentially saving time for health professionals, which can be used instead in care delivery. The study described in this protocol will evaluate the effectiveness of TRANSFoRm in improving the efficiency, time and costs of recruitment and data collection. The study will provide an evidence base for eHealth-supported recruitment and follow-up in primary care. Participant recruitment is scheduled to commence in February 2015 and be completed by May 2015. The scheduled end of follow-up data collection is July 2015. Reporting of results is expected in October 2015.

The study design has been tailored to the objectives of the evaluation and the characteristics of the GORD study. The evaluation focuses on the socioeconomic aspects of the system. The main goal is to ensure that TRANSFoRm can improve the efficiency, time and costs of conducting clinical research in primary care. The evaluation strategy draws on valid and reliable methods which have been widely used in health informatics research to assess the effectiveness of eHealth interventions [21]. The study will use quantitative and qualitative data collection techniques that enable triangulation of findings adding to the internal validity of the study. It will recruit urban, suburban and rural primary care centres in five countries and will employ culturally diverse study participants increasing the sample representativeness and thus external validity.

The evaluation will include patients with GORD, and otherwise eligible for the study, for whom a single clinic appointment was made during the recruitment period. This measure guards against the possibility that participating centres embark on an active programme of recruitment of potential participants rather than, as instructed, relying on opportunistic presentation. Local EHR and appointment datasets will be used to validate this process. An in-depth audit will be undertaken of any centre where the appointment rate lies more than two standard deviations from the within-country mean. In all other centres, a random selection of appointments created for GORD patients during the recruitment period will be audited by an evaluation team member in liaison with a local collaborator.

The study has some weaknesses. The scope of the economic analysis is limited to the care centre level. This practically means that we cannot assess the costs and benefits for all stakeholders in the project. However, patients will be able to provide qualitative feedback on the impact of the TRANSFoRm tools in follow-up interviews and a TAM survey. Another limitation is that the study timeline is relatively short to evaluate the long-term effects of the intervention, despite being sufficient to recruit the required number of participants and collect data to explore the evaluation aims. Considering that technology adoption is a complex process [22,23], the time from implementation to evaluation is relatively short to assess the performance of the TRANSFoRm system.

The protocol provides a reproducible process for conducting a summative evaluation of the TRANSFoRm system based on the GORD clinical trial. The evaluation study focuses on assessing the effectiveness of TRANSFoRm-supported recruitment and follow-up in primary care research compared with standard GP-led opportunistic recruitment. The study should provide useful information about the use of information technology to improve the efficiency, time and costs of recruitment and follow-up in primary care and is expected to provide an evidence base for future eHealth-supported recruitment initiatives.

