**Methods/design:**

This multi-centre, parallel-arm cluster randomised controlled trial will compare TRANSFoRm-supported with standard opportunistic recruitment. Participants will be general practitioners and patients with gastro-oesophageal reflux disease from 40 primary care centres in five European countries. Randomisation will take place at the care centre level. The intervention arm will use the TRANSFoRm tools for recruitment, baseline data collection and follow-up. The control arm will use web-based case report forms and paper self-completed questionnaires. The primary outcome will be the proportion of eligible patients successfully recruited at the end of the 16-week recruitment period. Secondary outcomes will include the proportion of recruited patients with complete baseline and follow-up data and the proportion of participants withdrawn or lost to follow-up. The study will also include an economic evaluation and measures of technology acceptance and user experience.

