**TRANSFoRm clinical trial workflow.**

The development of the clinical study workflow has been structured around a clinical study which acts as a use case for the evaluation of TRANSFoRm. The gastro-oesophageal reflux disease (GORD) study employs a randomised controlled trial design to answer the following question: “*What gives most symptom relief and improvement in quality of life in patients with GORD, on demand or continuous use of proton pump inhibitors?*”. Participants will be patients with GORD, aged 18–65 years old. The study will take place in five countries and will involve 16-week recruitment and 8-week follow-up. The follow-up time was chosen because proton pump inhibitor (PPI) treatment is known to have an effect after 2 weeks. Therefore, 8 weeks should be sufficient to detect any changes in symptoms and quality of life. The role of TRANSFoRm in this study is to identify prevalent and incident cases of GORD, randomise patients to on-demand or continuous use of PPI and follow up these patients using mobile or web applications and eCRF completed by GPs at primary care visits. Further details about the clinical study will be provided in a separate publication.

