### Intervention and control

Primary care centres allocated to the intervention arm will use the TRANSFoRm tools for participant recruitment, baseline data collection and follow-up. When visiting their GP, potentially eligible patients will be flagged by the system so that their GP can check for the first set of inclusion and exclusion criteria and, if appropriate, collect informed consent for further screening. Next, clinician-reported outcome measures (CROM) data from the patient’s health record will populate fields into the patient’s eCRF. The system will notify the GP about any missing data. Upon GP approval, the system will randomise patients to on-demand or continuous use of PPI. Participants will then receive information on how to fill out the PROM fields on their smartphone or the web. When participants return for the follow-up visit after 8 weeks, as stipulated in the clinical protocol, the CROM data is activated; the GP checks all prefilled fields and adds any missing data. If the participant does not attend the second visit, the GP will receive a reminder. PROM data is provided by the participants within 3 days from the second visit using the mobile/web application. Participants will receive reminders 2, 3 and 4 days after the visit, if the self-reported data is not provided.

Control centres will use standard GP-led opportunistic recruitment and data collection methods. Patients will be identified as potentially eligible by their GP after checking their health record during the consultation. The GP will check for the exclusion criteria, and, if the patient is still eligible, they will provide them with information about the study. Upon patient consent, the GP will complete the CROM fields and the patient will be randomised to on-demand or continuous use of PPI following the randomisation design for the GORD study (i.e. block randomisation containing four blocks based on age and gender). The patient will receive a questionnaire to complete either at the primary care centre or at home. Patients will be followed up using paper-based questionnaires.

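### The single-appointment inclusion rule does not exempt the 8-week study visit, so read literally it makes inclusion depend on having been recruited

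*Protocol article*

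**What the plan says.** The inclusion rule stands in the Discussion of the protocol article: the evaluation covers otherwise eligible GORD patients "for whom a single clinic appointment was made during the recruitment period". Its purpose follows: "This measure guards against the possibility that participating centres embark on an active programme of recruitment of potential participants". The same paragraph adds an audit based on local health-record and appointment data.

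The timetable is given where the Introduction describes the GORD study, which "will involve 16-week recruitment and 8-week follow-up". Under Intervention and control, the text on the TRANSFoRm arm reads "When participants return for the follow-up visit after 8 weeks, as stipulated in the clinical protocol, the CROM data is activated", and continues: "If the participant does not attend the second visit, the GP will receive a reminder". For the control arm it says "Patients will be followed up using paper-based questionnaires".

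The Abstract defines the outcome: "The primary outcome will be the proportion of eligible patients successfully recruited at the end of the 16-week recruitment period". The Primary outcome and Statistical methods sections likewise refer to eligible patients and do not mention an appointment restriction.

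**The concern.** Recruitment leads to a return visit. A patient recruited early in the window acquires a second appointment because of being recruited, while an otherwise identical patient who was not recruited does not. A rule that keeps only patients with one appointment in the window therefore conditions the analysis set on a consequence of the primary outcome. It takes recruits out of both numerator and denominator and leaves non-recruits in.

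If this happens equally in both arms, the observed rates and their difference shrink. If return visits are booked or attended more often in one arm, the comparison itself is biased. The text gives some reason to expect a difference: the return visit and the missed-visit reminder are spelled out only for the TRANSFoRm arm.

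**Working it through.** **Inputs from the protocol article.** Recruitment lasts 16 weeks and the return visit is at 8 weeks. The planned rates are 35% vs 20%. Sample size: 536 participants, 40 centres, 20 per arm, intra-cluster correlation 0.05, 5% significance, 90% power. At least 100 eligible patients are expected per centre. The accrual pattern, the attendance rate and the number excluded by the rule are not given.

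**The plan's own figure.** The usual two-sided formula without continuity correction needs 185 per arm before clustering.
- With m = 536/40 = 13.4 per centre, the design effect is 1 + 12.4 × 0.05 = 1.62. The total is then 600, and 536 gives 86.7% power.
- With m = 10 (not stated), the design effect is 1.45 and 2 × 185 × 1.45 = 536.5, which matches.

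I take 86.7% as the starting point at 13.4 per centre. At 100 per centre the design effect is 5.95 and power is 99.2%.

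**Share of recruits removed, f.** A recruit has the return visit inside the window if enrolled by week 16 − 8 = 8.
- Uniform accrual, full attendance: 8/16 = 50%.
- Linearly rising accrual: (8/16)² = 25%. Linearly falling accrual: 1 − (8/16)² = 75%.
- Uniform accrual, 80% attendance (assumed): 0.5 × 0.8 = 40%.
- Study visits not counted, or *single* meaning the index appointment: 0%.
- *Made* meaning booked, with the return visit booked at enrolment: nearly 100%.

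**Effect on the rates.** With true rate p, and ignoring repeat visits by non-recruits, the observed rate is p(1 − f)/(1 − pf). For f = 0.5:
- TRANSFoRm: 0.175/0.825 = 21.2%
- Control: 0.10/0.90 = 11.1%

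The observed odds are (1 − f) times the true odds. The odds ratio is therefore multiplied by (1 − f in TRANSFoRm)/(1 − f in control), starting from (0.35/0.65)/(0.20/0.80) = 2.15.

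Power is two-sided, with the reduced numbers and a recalculated design effect.

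| f, TRANSFoRm / control | Observed rates | Difference (points) | Odds ratio | Power, 13.4 per centre | Power, 100 per centre |
|---|---|---|---|---|---|
| 0 / 0 | 35.0 vs 20.0% | 15.0 | 2.15 | 86.7% | 99.2% |
| 25 / 25% | 28.8 vs 15.8% | 13.0 | 2.15 | 79.6% | 98.1% |
| 50 / 50% | 21.2 vs 11.1% | 10.1 | 2.15 | 66.9% | 94.1% |
| 75 / 75% | 11.9 vs 5.9% | 6.0 | 2.15 | 43.6% | 76.5% |
| 50 / 25% | 21.2 vs 15.8% | 5.4 | 1.44 | 23% | 43% |
| 25 / 50% | 28.8 vs 11.1% | 17.7 | 3.23 | not calculated | not calculated |

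Equal removal leaves the odds ratio unchanged; it shrinks the rates and their difference and costs power. Unequal removal distorts the odds ratio as well, in a direction that depends on which arm loses more recruits.

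**The case against.** Several points on the other side carry weight.

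- **Purpose.** The rule is aimed at appointments created in order to recruit. A patient returning for a study visit is already a participant, so that visit is not its target, and *a single clinic appointment* may be meant as one qualifying presentation per patient. This may well be the intention, but the text does not say so, and an analyst extracting the data would have to guess.
- **Scope.** The rule appears only in the Discussion, so its use in the primary analysis is inferred. That stands as a condition on the finding. Still, the sentence is worded as an inclusion rule for the evaluation.
- **Non-recruits.** Read literally, the rule also drops non-recruits who attend repeatedly. If half of them were dropped alongside half of the recruits, 35% vs 20% would be restored. But a background repeat rate shared by recruits and non-recruits cancels out of the formula. The bias disappears only if non-recruits lose as large a share as recruits, and nothing in the article supports that.
- **Power.** At the 100 or more eligible patients per centre that the plan expects, equal 50% removal still leaves 94% power. This stands: loss of power is the lesser problem.

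A reader might infer three stronger claims that the documents do not support:
- *About half of all recruits will be lost.* This needs uniform accrual, full attendance and study visits counting as clinic appointments; the article itself provides for missed visits.
- *The bias runs against TRANSFoRm.* The last row of the table runs the other way.
- *The planned effect is erased.* Removing 50% of TRANSFoRm recruits and no controls gives 21.2% vs 20.0%. But the article attributes the visit to the clinical protocol, and paper questionnaires describe how data are collected, not the absence of a visit.

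**Conclusion.** The rule is wrong as written. It has no exemption for the study visit and, taken literally as the definition of the primary denominator, it selects patients on a consequence of the outcome. Two conditions attach: that the rule governs the primary analysis, and that study visits count as appointments. The article settles neither.

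The size cannot be fixed from the documents. The share of recruits removed runs from 0% to nearly 100%, with 50% as an illustration under stated assumptions. The more serious risk is unequal removal between arms, because it biases the estimate at any sample size. Its direction is unknown.

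**What to change.** Reconcile the Intervention and control section, the Primary outcome section and the Discussion with one definition. The primary denominator is every eligible patient with at least one attended appointment in the recruitment window, counted once, with the first such appointment as the index. State that the 8-week study visit and any later appointment never exclude a patient.

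Rely on the appointment audit already described in the Discussion to detect active call-ins. The single-appointment rule adds little there, since a patient called in once still has exactly one appointment.

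The cost is a one-paragraph amendment and a changed extraction query. No new data are needed, because the health-record and appointment datasets are already to be used.

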### Primary outcome

The primary outcome measure is the proportion of eligible patients successfully recruited using the TRANSFoRm method compared to standard GP-led opportunistic recruitment. A record of all identified, screened and successfully recruited patients will be kept using data from GP systems. The percentage of those recruited in the trial will be compared to identify whether TRANSFoRm yields a higher number of recruited patients compared to standard GP recruitment.

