### Statistical methods

The percentage of patients recruited to the study for the intervention and control groups will be calculated using descriptive statistics with 95% confidence intervals. These will be presented separately for each site, country and overall. The proportion of eligible participants recruited will be compared between groups using logistic regression, adjusted for clustering by centre by using generalised estimating equations (CI 95%, *P* < .05). Between-group differences in recruitment rate will be analysed using chi-square tests. This method will be also applied to compare the percentage of participants with complete data and the percentage of eligible patients who were recruited but later withdrew or lost to follow up.

Descriptive statistics will be used to outline the relative proportion of participants who were satisfied or dissatisfied with the TRANSFoRm tools as per item on the TAM questionnaire. Quantitative data will be analysed in STATA (v13) using an intention-to-treat approach.

Data from the user experience interviews will be audio-recorded, transcribed verbatim and analysed thematically using Ritchie and Spencer’s framework analysis approach [17].

The study has been designed and will be reported in CONSORT-compliant format [18].

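### Taken literally, the single-appointment rule drops recruits whose 8-week return visit falls within the 16-week recruitment period, so the primary denominator depends on the outcome

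*Protocol article*

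**What the plan says.** The rule is in the Discussion of the protocol article. The evaluation takes in patients with reflux disease who are otherwise eligible and "for whom a single clinic appointment was made during the recruitment period". The next sentence gives its purpose: "This measure guards against the possibility that participating centres embark on an active programme of recruitment". Local record and appointment data are to be used to check the process. Centres with outlying appointment rates get an in-depth audit, and elsewhere a random selection of appointments is audited.

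Three other places bear on it.

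- **Timetable.** The text under the clinical trial workflow says that the study "will involve 16-week recruitment and 8-week follow-up".
- **Visits.** Intervention and control describes the TRANSFoRm procedure with the words "When participants return for the follow-up visit after 8 weeks, as stipulated in the clinical protocol", and adds a reminder to the GP if the patient does not attend. For the control arm the section says only "Patients will be followed up using paper-based questionnaires".
- **Primary outcome.** That section states: "The primary outcome measure is the proportion of eligible patients successfully recruited". It also states: "A record of all identified, screened and successfully recruited patients will be kept using data from GP systems". It sets no limit on the number of appointments.

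**The concern.** A patient recruited at an ordinary consultation in week 4 is due back in week 12. Both dates are inside the 16 weeks, so that patient no longer has a single appointment. A patient who was seen once and not recruited still has one. Being recruited therefore raises the count that decides who is analysed, and the rule takes successes out of both the numerator and the denominator of the primary proportion.

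The rule also serves its stated purpose poorly. A patient called in once in order to be recruited has one appointment and stays. A patient who came of their own accord and then returned for follow-up is dropped. Ordinary repeat attenders are dropped too. The article gives no appointment rates, so the size of that last loss cannot be stated.

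At stake are both arms' recruitment percentages, the 15-point difference in which the hypothesis is worded, and power. If the return visit is more common in one arm, the odds ratio is at stake as well.

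**Working it through.** **Inputs from the article.** Rates 20% and 35%; intra-cluster correlation 0.05; 20 centres per arm; 536 participants for 90% power; at least 100 eligible patients per centre (Sample size). Recruitment 16 weeks, follow-up 8 weeks.

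**Assumption.** Recruitment is uniform over the 16 weeks, so a fraction f = 8/16 = 0.5 of recruits have their return visit inside the period.

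**The plan's own figure.** 536/40 = 13.4 patients per centre. Design effect = 1 + 12.4 × 0.05 = 1.62. Effective size per arm = 268/1.62 = 165.4. Standard error = √[(0.2 × 0.8 + 0.35 × 0.65)/165.4] = 0.0484, and 0.15/0.0484 = 3.10. Two-sided 5% power = Φ(3.10 − 1.96) = 87%. A one-sided 5% test with continuity correction needs 523 to 528 patients for 90% power, within 3% of 536. The article does not state sidedness. I use two-sided tests below; the point does not depend on this.

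**Effect of the rule on a rate.** If a fraction f of recruits is removed from numerator and denominator, p becomes p(1 − f)/(1 − pf).

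*(a) Visit in both arms, f = 0.5*
- Control: 0.10/0.90 = 11.1%. TRANSFoRm: 0.175/0.825 = 21.2%. Difference 10.1 points instead of 15.0.
- The odds become p(1 − f)/(1 − p), so f cancels from the ratio. Before: 0.538/0.25 = 2.15. After: 0.269/0.125 = 2.15.
- Power at 13.4 per centre: 12.06 and 11.05 patients per centre remain, the effective sizes are 155.3 and 147.1, the standard error is 0.0421, and 0.101/0.0421 = 2.40. Power is 67%, down from 87%.
- Power at 100 per centre: effective sizes go from 336.1 per arm to 330.3 and 325.1, and power from 99% to 94%.

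*(b) Visit only in the TRANSFoRm arm*

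| TRANSFoRm recruits removed | TRANSFoRm v control | Odds ratio |
|---|---|---|
| 25% | 28.8% v 20.0% | 1.62 |
| 50% | 21.2% v 20.0% | 1.08 |
| 75% | 11.9% v 20.0% | 0.54 |

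At 50% and 13.4 per centre, the standard error is 0.0459 and 0.0121/0.0459 = 0.26. Two-sided power, counting both tails, is about 6%. The difference is zero when f = (0.35 − 0.20)/(0.35 × 0.80) = 53.6%, and it reverses above that.

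*(c) A booking counts as an appointment made.* If the follow-up visit is booked at enrolment, nearly every recruit has two appointments and both rates fall towards zero.

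**The case against.** The strongest reply is that the rule was never meant to count follow-up visits. Its stated purpose concerns potential participants who present opportunistically, and someone returning at 8 weeks is already enrolled. One presenting appointment per patient, before enrolment, is a tenable reading and loses no recruit through follow-up. Case (c) would leave almost nothing to analyse, which suggests that the literal reading was not intended. The sentence also sits in a Discussion, while Primary outcome and Statistical methods carry no such limit. This may well describe the intention. But the article calls the rule a measure with a purpose and never writes the index-visit version, so an analyst who followed the text would build the wrong set.

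A reader might infer that the rule will erase the treatment effect. The article does not support that. Equal removal leaves the odds ratio of the planned logistic model unchanged. Erasure needs a visit confined to one arm, or counting by booking. The visit is attributed to the clinical protocol, under which both arms' patients are enrolled, and the control sentence names a questionnaire mode without saying that there is no visit.

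A reader might also take 87% to 67% as the power loss. That holds at 13.4 patients per centre. The outcome is defined over eligible patients, of whom at least 100 per centre are expected, and there the loss is 99% to 94%.

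Nor is there a firm clash with the statement "Quantitative data will be analysed in STATA (v13) using an intention-to-treat approach". That principle concerns analysis by allocated arm, and an eligibility rule does not by itself contradict it. Likewise, a record of all recruits is compatible with a narrower analysis set.

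**Conclusion.** The point holds as a fault in a stated rule. Read literally, the appointment limit selects the primary denominator on the outcome, and it cannot be reconciled with a primary outcome over all eligible patients.

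With uniform accrual and equal removal of half the recruits, the absolute difference shrinks by about a third (10.1 instead of 15.0 points). Both percentages are too low, some power is lost, and the odds ratio is intact. Bias in the odds ratio, up to loss or reversal of the effect, arises only if visits differ by arm. The article leaves this open and does not establish it. Near-total loss of recruits arises only if visits booked at enrolment count. It should be corrected because the primary denominator rests on it and the change is small.

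**What to change.** Replace the sentence in the Discussion with a rule of this kind: each otherwise eligible patient with at least one non-trial appointment in the 16 weeks is counted once, as recruited or not recruited by the end of week 16, whatever the number of appointments. Visits generated by the trial never count in any appointment rule. Reconcile this with Primary outcome, and state in Intervention and control whether the 8-week visit applies in both arms.

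Keep the planned audit as the check on active recruitment. Add a sensitivity analysis that excludes patients whose index appointment the audit shows was created to invite them.

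The cost is a sentence in the protocol and a change to the appointment query. The downside is a weaker formal guard: outside outlier centres the audit only samples appointments, so the sensitivity analysis cannot find every invited patient.
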